**3.3 Randomization and blinding**

**3.3.1 Method of randomization**

In both trials, computer-aided and concealed block randomization with pre-stratification by center and presence of a uncomplicated or complicated UTI will be performed. The Coordinating Center (AMC) prepares drug randomization lists for each study site in advance. All eligible and consenting patients will be randomly allocated to either:

- antibiotic prophylaxis (RCT A and B)

- non-antibiotic prophylaxis: cranberries (RCT-A),

lactobacilli (RCT-B)

- - 1. **Method of blinding**

In each trial two active compounds will be compared. Antibiotics are produced as tablets and non-antibiotics as capsules. Therefore, the “double-dummy”-method is used. Each patient receives 1 tablet and 2 capsules daily, but only one of them (the tablet or the capsules) contains the active substance. Drug packages are labelled with the Study Identification code (SID) by a central pharmacy. Afterwards packages are distributed to the hospital pharmacies of the participating centers. Neither the blinded study team nor the patient will be informed of the treatment until the data collection phase has been completed.

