**4 Study population**

- 1. **Recruitment and screening method**

Seven Dutch hospitals participate; three university hospitals (Academic Medical Center/Amsterdam, Academic Hospital Maastricht/Maastricht, University Medical Center/Utrecht) and four non-university hospitals (Onze Lieve Vrouwe Gasthuis/Amsterdam, Sint Lucas Andreas Hospital/Amsterdam, Maasland Hospital/Sittard, and Westfries Gasthuis/Hoorn). Urologist, infectious disease specialists or geriatricians from the above-mentioned centers determine patient eligibility and seek informed consent. The specialist will pass contact information from all eligible patients to the study coordinator. The specialist also gives an information letter and two informed consent forms (with one self-addressed envelope) to the patient. Afterwards, the study coordinator contacts the patient and checks if the patient really fulfils the entry criteria. Then the patient will be asked for informed consent. After informed consent the patient has to give or send one signed informed consent form back to the study coordinator, the other stays with the patient.

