**5.5 Compliance checking method**

The compliance will be measured monthly (together with the collection of the vaginal swabs and urine and faeces samples) by pill counts. In addition, vaginal and faecal cultures will be examined on the presence of lactobacilli, and urine concentrations of TMP-SMX and proanthocyanidins will be determined.

1. **Clinical and laboratory evaluations**
   1. **Clinical evaluations**

During the course of the study, a set of Case Report Forms (CRFs) is completed. At t= 0 (at inclusion) demographic data (age, place of residence [for example nursing home], sexual activity, relevant medical history and concomitant diseases, number of UTIs in the previous year, medication, known urinary tract abnormalities, urinary catheter use) will be collected by the study coordinator.

Each month thereafter, during the 15 months of follow up, a questionnaire is sent to the patient. On those questionnaires, other relevant parameters concerning possible adverse events (e.g., allergic reactions, skin rash, gastrointestinal disturbances), possible interactions with other medication, and the medical history (change of place of residence, new concomitant diseases, medication change, pregnancy, hospital admissions, invasive procedures, operations, urinary catheter placement or removal) during the follow-up will be noted.

Quality of life questionnaires (concerning the general well-being and related to the disease) will be administered at baseline and 6, 12 and 15 months post-randomization.

- 1. **Laboratory evaluations**

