**8.2.1 General approach**

The data-analytic approach involves data-quality management and data-analysis. Flawless data-files will be ensured by double data-entry procedures. Data-analysis proper will follow four steps: (1) univariate data checks to assess distributions and identify potential outlying values, (2) relevant bivariate analyses using tables and scatter plots, to assess crude associations between co-variables and the outcomes, and among co-variables, (3) stratified analyses and Kaplan-Meier analysis aimed at the treatment effects, (4) (Cox) regression models.

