**8.2.2 Primary outcome**

Data will be analysed according to the intention to treat principle. In the two trials, the (cumulative) proportions of symptomatic UTIs at 12 months will be compared between the groups (non-inferiority part), and the time intervals to the first occurrence of faecal and urine antibiotic resistance will be compared between the two groups using standard survival time analysis techniques (resistance part).

- - 1. **Secondary outcome**

Data differences between the proportions showing adverse effects at 12 months will be analysed similarly as the primary ones, except the quality of life measures at 12 months, for which multivariable linear regression will be used. Since antibiotic resistance is a gradual phenomenon, a more refined analysis using ordinal logistic regression, will assess differences in proportions of patients at different concentrations of antibiotic resistance between the treatment groups. Other secondary analyses pertain to all microbiological outcomes at 15 months.

In both trials we will also separately analyse the patients with uncomplicated versus complicated UTIs.

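### The primary comparison of 12-month proportions is not tied to the factors that stratify randomisation; the cost is small, errs on the conservative side, and is free to remove.

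*Protocol*

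**What the plan says.** - **Randomisation (Protocol, section 3.3.1):** "concealed block randomization with pre-stratification by center and presence of a uncomplicated or complicated UTI will be performed". The section on recruitment states "Seven Dutch hospitals participate".
- **Primary comparison (section 8.2.2):** analysis is by intention to treat, and "the (cumulative) proportions of symptomatic UTIs at 12 months will be compared between the groups". No strata, covariates or estimator are named. Resistance is to be compared by standard survival methods, again without strata.
- **General approach (section 8.2.1):** step 2 uses tables and scatter plots "to assess crude associations between co-variables and the outcomes, and among co-variables". Step 3 is "stratified analyses and Kaplan-Meier analysis aimed at the treatment effects". Step 4 is (Cox) regression. The strata in step 3 are not identified, and no step is named as the one that decides non-inferiority.
- **Baseline data (section 6.1, Clinical evaluations):** the "number of UTIs in the previous year" is recorded. No analysis mentions it.
- **Patient groups (end of section 8.2, under secondary outcomes):** "In both trials we will also separately analyse the patients with uncomplicated versus complicated UTIs". No interaction estimate is mentioned.

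**The concern.** Blocking within strata forces the arms to be balanced on the stratum factor, so a prognostic factor no longer adds to the sampling variation of the difference between arms. An unadjusted standard error still counts that variation. The interval is then a little wider than the design warrants, and in a non-inferiority test its width decides the outcome.

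The second matter is how the complicated and uncomplicated groups will be read. Two separate analyses, one of which clears a margin while the other does not, say little about whether the treatment effect differs between them. The direct answer is the difference between the two stratum-specific effects, with its own interval.

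**Working it through.** **1. Do the plan's own figures rely on adjustment?**

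Inputs from section 8.1: success 95% v 85%, one-sided alpha 0.05, power 80%, 130 analysable women per arm.

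Two-proportion formula, with mean proportion 0.90:

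n = [1.645·√(2·0.90·0.10) + 0.842·√(0.95·0.05 + 0.85·0.15)]² / 0.10² = 110.2, so 111.

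With continuity correction: (110.2/4)·[1 + √(1 + 4/(110.2·0.10))]² = 129.5, so **130**, as stated.

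Resistance, 30% v 15%, 130 per arm, two-sided 0.05, continuity-corrected: (0.15 − 1/130 − 1.96·0.0518)/0.0510 = 0.80, which gives **78.8%**, as stated.

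Both are unadjusted formulas. The design takes no credit for adjustment, so leaving it out costs none of the planned power. (That 130 comes from a formula for detecting a difference is a separate matter, not pursued here.)

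**2. What would adjustment for complicated/uncomplicated UTI gain?**

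The documents give neither the share of complicated patients (w) nor the gap in success between the strata (d). Both are assumed. With overall success p and arms balanced within strata:

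variance ratio VR = 1 − w(1−w)d² / [p(1−p)]

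Power is for 130 per arm, the margin of section 8.1 read as 10 percentage points, one-sided 0.05, and equal true success in both arms. The unadjusted standard error is SE = √[2p(1−p)/130].

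- Adjusted power: Φ(0.10/(SE·√VR) − 1.645)
- Unadjusted power: Φ((0.10 − 1.645·SE)/(SE·√VR))
- True one-sided alpha of the unadjusted test: Φ(−1.645/√VR)

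| p | d | w | VR | Unadjusted | Adjusted | True alpha, unadjusted |
|---|---|---|---|---|---|---|
| 85% | 10 points | 20% | 0.988 | 73.1% | 73.5% | 0.049 |
| 85% | 10 points | 50% | 0.980 | 73.2% | 73.7% | 0.048 |
| 85% | 20 points | 20% | 0.950 | 73.5% | 74.9% | 0.046 |
| 85% | 20 points | 50% | 0.922 | 73.8% | 76.0% | 0.043 |
| 87% | 10 points | 20% | 0.986 | 77.6% | 77.9% | 0.049 |
| 87% | 20 points | 50% | 0.912 | 78.5% | 80.7% | 0.043 |

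Worked row: p = 0.85, d = 0.20, w = 0.50. VR = 1 − 0.25·0.04/0.1275 = 0.922. SE = √(2·0.1275/130) = 0.0443. Adjusted: 0.10/(0.0443·0.960) − 1.645 = 0.707, so 76.0%.

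Before rounding, the gains run from 0.3 to 2.2 points. At 95% success there is almost nothing to gain (d = 10 points, w = 20%: 98.2% to 98.3%).

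**3. Could the full set of strata be used?**

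7 centres × 2 types = 14 strata per trial; 280/14 = 20 women per stratum, 10 per arm. Expected women with a UTI per arm: 130·0.05 = 6.5 at 95% success and 130·0.15 = 19.5 at 85%. That is 0.5 to 1.4 per stratum and arm, so a full centre-by-type stratification would be sparse.

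**4. What can the two separate analyses show?**

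Assume half the women are in each group (65 per arm). At 85% success in both arms and both groups, the SE of one group's difference is √(2·0.1275/65) = 0.063. Power against a 10-point margin is Φ(0.10/0.063 − 1.645) = 48%; at 87% success it is 52%. For a group holding 20% of the women (26 per arm) the figures are 26 to 28%.

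The difference between the two group effects has SE √2·0.063 = 0.089, so a 95% half-width of 1.96·0.089 = 17 points. The interaction estimate will be imprecise, and its interval shows this where two separate verdicts would hide it.

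**The case against.** The strongest reply is that covariate lists and stratified estimators usually belong in the statistical analysis plan, which is not at hand, and that section 8.2.1 already plans stratified analyses of the treatment effect. This stands as far as missing detail goes. What remains is that the protocol does fix a primary comparison and a separate analysis by UTI type, and links neither to its own randomisation scheme.

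Four stronger readings are tempting, and the text supports none of them:

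- **The strata are ignored.** Section 8.2.2 does not name them, but step 3 of section 8.2.1 does not exclude them.
- **Covariates are screened on their association with outcome.** Step 2 is descriptive. No rule says that it selects covariates for step 4.
- **The analysis by UTI type spends the primary comparison's precision, or promises a non-inferiority verdict per group.** It is one prespecified split on a stratification factor, additional to the primary comparison, and no margin is announced for it.
- **False non-inferiority becomes more likely.** The unadjusted test is conservative, with a true alpha of about 0.043 to 0.049 in the cases above.

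It is also fair that the prior-year UTI count is not a randomisation factor. Entry requires at least three episodes, which narrows its range, and the documents give no evidence of its prognostic strength.

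**Conclusion.** The point holds as a low-cost improvement, not as an error that threatens the conclusion. The primary comparison is stated without the randomisation factors, and the stratified analyses elsewhere are neither tied to those factors nor made primary.

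The size depends on assumed inputs: a stratum gap of 10 to 20 points, a complicated share of 20 to 50%, and 85 to 87% success in both arms. Under these, the variance ratio is 0.91 to 0.99 and the gain about 0.3 to 2.2 power points at 130 per arm. A smaller gap, or success near 95%, makes it negligible.

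For the analysis by UTI type, the gain is in interpretation: one estimate of how far the effect differs, in place of two results that a reader may wrongly set against each other.

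**What to change.** 1. In section 8.2.2, define the primary estimate as the 12-month risk difference stratified by or adjusted for complicated/uncomplicated UTI (Mantel-Haenszel or a standardised logistic model), and compare its confidence limit with the margin. Pool centres, or include centre only if event numbers allow, by a rule set before unblinding. Prior-year UTI count may be added as a prespecified covariate.
2. Stratify the survival analysis of resistance by the same factor.
3. In section 8.2.1, state that step 2 is descriptive and does not choose covariates for the primary model.
4. Accompany the separate complicated and uncomplicated analyses with a treatment-by-stratum interaction estimate and stratum-specific confidence intervals, without a verdict per group.

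All the variables are already collected, so the cost is wording, a little analysis work and possibly the pooling of small centres.

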**2 Study objectives and endpoints**

**2.1 Study objectives**

**2.1.1 Primary objectives**

- To determine if non-antibiotic prophylaxis is a non-inferior treatment in the prevention of recurrent symptomatic UTIs compared to the currently standard antibiotic prophylaxis in pre- and post-menopausal women (non-inferiority trial)
- To assess if non-antibiotic prophylaxis reduces the selection of antibiotic resistant micro-organisms in urine and faeces compared to currently standard antibiotic prophylaxis in pre- and postmenopausal women
  - 1. **Secondary objectives**
- To evaluate if non-antibiotic prophylaxis compared to antibiotic prophylaxis in pre- and post-menopausal women lead to differences in the:

- incidence of asymptomatic bacteriuria

- incidence of other (non-urinary tract) infections

- incidence of adverse events

- quality of life

- To evaluate the costs and cost-effectiveness of non-antibiotic prophylaxis compared to antibiotic prophylaxis in the prevention of recurrent UTIs in pre- and post-menopausal women.

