**3 Methodology**

- 1. **Study design**

The NAPRUTI study consists of two trials: RCT-A and RCT-B. Premenopausal women will be included in RCT-A, postmenopausal women in RCT-B. Both trials are multi-center, randomized double blind clinical trials with a follow-up time of 15 months.

Both trials consist of two parts: part one deals with UTI recurrence (non-inferiority part); part two aims to show a difference with respect to the development of bacterial drug resistance.

- 1. **Study duration**

Both trials will recruit 280 women. Patient enrolment is anticipated to last 2 years. After randomization patients will be followed for 12 months during which they will receive study medication and 3 months afterwards (“wash-out”-period). Total study duration will be 48 months.

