At t= 0 and monthly thereafter, during the one year intervention period and the three months follow-up after stopping the intervention, material for culture will be sent to the patients. Vaginal swabs as well as samples from urine and faeces have to taken each month. Urine samples and faecal samples will be quantitatively analysed for the presence and degree of antibiotic (TMP-SMX) resistant micro-organisms. In addition, the vaginal swabs (2x) will be examined on the presence of lactobacilli and to one of the Gram stained swabs a Nugent score will be given. The scoring system examines vaginal cells at random and applies a 0-3 score for normal (dominated by Gram-positive bacilli resembling lactobacilli), 4-6 for intermediate (lactobacilli present along with Gram-variable rods), and 7-10 for bacterial vaginosis (no lactobacilli seen and cells colonized by Gram-negative rods). Urine samples will be examined for the presence of proanthocyanidins.

All samples (urine, faeces and vaginal swabs) will be analysed in the microbiology laboratory of the University Hospital Maastricht. To prevent growth of uropathogens in urine samples during transportation, dipslides will be used: a dipslide will be dipped in a fresh voided urine sample according to the manufacturer’s instructions. Dipslide, vaginal swabs (in transport medium) and faecal samples (1-2 gram) will be sent to the microbiological laboratory in Maastricht. The antibiotic susceptibility of the isolated resistant micro-organisms in the urine and faecal samples will be determined as a microbroth or Agar dilution method according to the SWAB standard [seeResistentie surveillance standaard SWAB 1999]. All other infections during the intervention and the follow-up period will be registered. Only in case of a symptomatic UTI, the patient will be asked to send a urine-dipslide to the microbiological laboratory in Maastricht.

For details about specimen collection requirements and laboratory tests: see table 2.

| **Specimen Type** | **When** | **Determination** | **Test** | **(Interpretation of)**  **results** |
| --- | --- | --- | --- | --- |
| Urine | Baseline, each month during follow-up + in case of symptomatic UTI | - Culture (max. 2 m.o.)  - Concentration TMP-SMX  - Analysis TMP-SMX -resistant m.o.  - Concentration proanthocyanidins | Dipslide  Microbroth dilution | Positive: >/=10³ CFU/ml urine  R, S, MIC (criterions NCCLS) |

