### Asymptomatic bacteriuria: Presence of at least 10e3 CFU/ml of one or two micro-organisms in a culture of a clean voided urine sample isolated from a patient without symptoms of a UTI.

### Symptomatic UTI: Presence of bacteriuria (10e3 CFU/ml of one or two micro-organisms) in combination with at least one of the following symptoms: dysuria, frequency, haematuria, lower abdominal pain, flank pain or unexplained fever.

Complicated UTI: UTI in all men, pregnant women, women with structural or functional abnormalities of the urinary tract, or who are immunocompromised (e.g. having diabetes) or use immunosuppressive drugs.

Uncomplicated UTI: UTI without characteristics of a complicated UTI.

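### Section 8.2.3 ties asymptomatic bacteriuria only to month 15, three months after prophylaxis stops, so no stated analysis cleanly compares it during prophylaxis

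*Protocol*

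**What the plan says.** Protocol sections 2.1.2 and 2.2.2 both list "incidence of asymptomatic bacteriuria" first among the secondary objectives and endpoints. The objective is to learn whether non-antibiotic and antibiotic prophylaxis differ on it. Appendix I defines the condition by culture, in a woman without UTI symptoms: "Presence of at least 10e3 CFU/ml of one or two micro-organisms in a culture of a clean voided urine sample". A single culture is enough.

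Section 3.2 sets the periods: women are "followed for 12 months during which they will receive study medication and 3 months afterwards", and the second period is called the wash-out. Section 6.2 sets the sampling: "At t= 0 and monthly thereafter, during the one year intervention period and the three months follow-up after stopping the intervention", with urine, faeces and vaginal swabs taken each time.

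For the resistance part, section 8.2.2 states that "the time intervals to the first occurrence of faecal and urine antibiotic resistance will be compared between the two groups using standard survival time analysis" methods. Section 8.2.3 then covers the secondary outcomes. It names 12 months for adverse effects and quality of life. For resistance it adds "a more refined analysis using ordinal logistic regression, will assess differences in proportions of patients at different concentrations of antibiotic resistance between the treatment groups", with no time point. It closes the microbiology with "Other secondary analyses pertain to all microbiological outcomes at 15 months". No other sentence gives asymptomatic bacteriuria a time point or an analysis.

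**The concern.** The objective concerns what happens to bacteriuria under two kinds of prophylaxis. The one time point attached to it lies three months after both kinds have stopped. A difference that exists during treatment and fades afterwards would be missed or diluted, and the report could say that the groups do not differ when the data already collected would show that they do. An analysis plan that follows this sentence faithfully would inherit the mismatch.

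The monthly urine cultures taken during treatment bear most directly on this endpoint. The protocol states no use of them for it.

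**Working it through.** **1. Schedule.** Inputs: 12 months on study medication and 3 months after it (section 3.2); monthly samples in both periods (section 6.2). This gives 12 on-treatment and 3 off-treatment rounds after baseline. Month 15 is the last off-treatment round. If all 15 are pooled, 3/15 = 20% are off treatment.

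**2. Two readings of month 15.** Section 8.2.2 uses its 12-month time point for a cumulative proportion of symptomatic UTIs, so the 15-month time point may be meant the same way.

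- *Point value.* One off-treatment prevalence, which is not an incidence. For scale, if cultures were independent (an assumption), a per-culture prevalence p gives a 12-culture cumulative incidence of 1 − (1 − p)^12: 46% for p = 5%, 72% for 10%, 86% for 15%. These are different quantities.
- *Cumulative.* An incidence, but over two periods with different exposure.

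**3. The protocol's only microbiological power figure.** Section 8.1 gives 78.8% for resistance of 30% v 15%. With n = 130 per arm, two-sided 0.05 (the sidedness is my assumption) and a continuity correction, the mean proportion is 0.225:

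z = [0.15 − 1/130 − 1.96 × √(2 × 0.225 × 0.775/130)] / √[(0.30 × 0.70 + 0.15 × 0.85)/130] = (0.1423 − 0.1015)/0.0510 = 0.80, so power is 78.8%.

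The figure reproduces. It concerns resistance, not bacteriuria; I borrow its contrast below for illustration only.

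**4. Illustration, point-value reading.** Power = Φ(d/SE − 1.96), unpooled variance, no continuity correction, n = 130 per arm.

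- One on-treatment sample, 30% v 15%: 0.15/0.0510 = 2.94; power 84%.
- Mean of 12 on-treatment samples, variance multiplied by r + (1 − r)/12, with assumed within-woman correlation r = 0.3, 0.5, 0.7: factors 0.358, 0.542, 0.725; power 99.8%, 97.9%, 93.3%.
- Month 15, higher arm held at 30%, by the assumed share of the difference that persists:

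| Share persisting | Contrast | Power |
|---|---|---|
| 75% | 30% v 18.75% | 57% |
| 50% | 30% v 22.5% | 28% |
| 25% | 30% v 26.25% | 10% |
| 0% | 30% v 30% | 2.5% (in that direction) |

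For 20% v 10%: one on-treatment sample 63%; 12 samples 97% to 76% for r = 0.3 to 0.7; month 15 with half persisting (20% v 15%) 18%.

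**5. Illustration, cumulative reading.** Assume independent cultures, 5% v 3% per culture on treatment, and both arms at 5% after stopping.

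- Months 1 to 12: 1 − 0.95^12 = 46.0% v 1 − 0.97^12 = 30.6%; difference 15.3 points; power 73%.
- Months 1 to 15: 1 − 0.95^15 = 53.7% v 1 − 0.97^12 × 0.95^3 = 40.5%; difference 13.2 points; power 57%.

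The difference shrinks by the factor 0.95^3 = 0.857. The loss is milder than under the point-value reading.

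**The case against.** The strongest reply is that the sentence is an addition, not a replacement. It says that *other* analyses cover *all* microbiological outcomes, and these include resistance, which already has its own analyses. It may therefore only extend the microbiology to the end of the wash-out, leaving the on-treatment bacteriuria analysis to a statistical analysis plan that is not shown. The general approach in section 8.2.1 (stratified, Kaplan-Meier and Cox analyses) is not limited to primary outcomes either. This has force: a model left unnamed for a secondary endpoint would be no fault. But the protocol does not stay silent on timing. It fixes one time point that covers bacteriuria, and it states no on-treatment bacteriuria analysis to which month 15 would be added.

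A reader might infer four stronger things, which the document does not support:

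- *Month 15 is the only secondary microbiological analysis.* It is not; the ordinal resistance model is stated just before it, without that restriction.
- *The on-treatment cultures go unused.* They do not. The urine and faecal cultures supply time to first resistance, and section 5.5 uses the monthly samples for compliance checks.
- *Bacteriuria will certainly be judged on one sample.* That is one of two readings, and the cumulative one suits an endpoint named as an incidence better.
- *RCT-B's lactobacillus mechanism is a listed comparison made too late.* Lactobacilli and the Nugent score are laboratory and compliance measures, not listed endpoints.

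The objection to the power figures also stands: they borrow a resistance contrast and use correlations, persistence shares and culture rates that the protocol does not give.

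**Conclusion.** The point holds for asymptomatic bacteriuria. Section 8.2.3 attaches a listed secondary endpoint only to month 15, three months after prophylaxis ends, and does not say whether this is a point prevalence or a cumulative incidence. The first is off treatment; the second mixes the two periods. Neither cleanly compares bacteriuria during prophylaxis. This conclusion rests on the text alone.

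The size cannot be known from the protocol. Under the stated assumptions the loss runs from moderate (73% to 57% on the cumulative reading) to severe (84% to 28% on the point reading with half the difference persisting). If the on-treatment difference persisted in full after stopping, the off-treatment cultures would not dilute it, although a single sample would still discard the repeated measurements. The primary endpoints are not affected. The point should be corrected, but it does not threaten the main conclusions of the trial.

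**What to change.** State in section 8.2.3 that asymptomatic bacteriuria will be compared between the randomised groups over the 12-month intervention period, using all scheduled monthly urine cultures, with the baseline culture as a covariate. Several methods would serve: a repeated-measures logistic or GEE model for presence at each visit, or cumulative incidence or time to first episode. One should be named in advance. State separately that months 13 to 15 form a post-treatment (wash-out) analysis, and whether its result is a month-15 prevalence or an incidence over those three months.

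The cost is a change of wording and slightly more analysis work. The samples are already scheduled, so no extra cultures, visits or women are needed, and the month-15 analysis is kept under a label that says what it measures.
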